### **4.3 Subject Completion/Withdrawal**

Subjects may withdraw from the study at any time without prejudice to their care. They may also be discontinued from the study at the discretion of the Investigator for lack of adherence to study treatment or visit schedules. The Investigator or the Sponsor may also withdraw subjects who violate the study plan, or to protect the subject for reasons of safety or for administrative reasons. It will be documented whether or not each subject completes the clinical study. If the Investigator becomes aware of any serious, related adverse events after the subject completes or withdraws from the study, they will be recorded in the source documents and on the CRF.

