#### **4.3.1 Early Termination Study Visit**

Subjects will be withdrawn if their eligibility status changes such that it is no longer safe for them to complete the fMRI. If subjects choose to withdraw from the study, all of their longitudinal data will be excluded from the final data analysis. If initial baseline assessments are complete a group level comparison will be conducted with this current PPCS-CI data and the already collected TYP-CI and control data.

---

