## **6 STATISTICAL CONSIDERATIONS**

### **6.1 Primary Endpoint**

The primary endpoint will be the change in composite clinical parameters of near point of convergence and positive fusional vergence between the initial assessment and the outcome visits.

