#### **6.3.2 Efficacy Analysis**

The primary analysis will be based on an intention to treat approach and will include all subjects randomized at their initial assessment.

The primary efficacy endpoint will be the change in composite clinical parameters of near point of convergence and positive fusional vergence between the initial assessment and the outcome visits. A repeated measures ANOVA will be used to assess the clinical parameters as well as the chi-squared test using predetermined published optometric benchmarks for improvement.

Secondary endpoints will include the rate of symptom remediation in OBVAT+SCC group compared to SCC alone, change in vision function, and fMRI measures between the start and end of the treatment phase.

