### **6.4 Sample Size and Power**

We expect that approximately 200 subjects will be enrolled to produce 150 subjects who finish the protocol and data does not suffer motion artifacts which can cause data to be

---

omitted from group level analyses. The sample size calculation was performed using paired *t*-tests with equal variance for TYP-CI patients from both placebo therapy and OBVAT. Our published pilot data had an estimated correlation of -0.3, 0.9, -0.4, and -0.3 for CISS, NPC, PFV, beta weight from oculomotor vermis respectively. This gave a standard deviation of the difference (OBVAT- placebo/sham therapy) to be 19, 2, 19, and 27. Assuming 80% power, Alpha= 0.05, and adjusting for an 80% retention rate and 15% data loss due to motion artifacts during fMRI experiments, results in the number of subjects needed to be 37, 6, 37, 46 respectively. Using the maximum sample size for all conditions and to be satisfied, yields a cohort size of 46 per arm. We rounded the number of participants to 50 PPCS-CI for each arm.

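### Section 4.3.1 excludes withdrawn subjects' longitudinal data from the final analysis, which contradicts the intention-to-treat primary analysis in section 6.3.2

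*Protocol*

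**What the plan says.** Two rules in the protocol decide who enters the efficacy analysis.

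- Section 6.3.2: "The primary analysis will be based on an intention to treat approach and will include all subjects randomized at their initial assessment".
- Section 4.3.1: "If subjects choose to withdraw from the study, all of their longitudinal data will be excluded from the final data analysis".

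Section 4.3.1 then keeps the baseline values of these subjects for a different purpose: "If initial baseline assessments are complete a group level comparison will be conducted with this current PPCS-CI data", set against the TYP-CI and control data already collected.

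Section 6.1 defines the endpoint: "The primary endpoint will be the change in composite clinical parameters of near point of convergence and positive fusional vergence", measured from the initial assessment to the outcome visits.

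Two other routes out of the study are described. Section 4.3.1 says "Subjects will be withdrawn if their eligibility status changes such that it is no longer safe for them to complete the fMRI". Section 4.3 says of subjects: "They may also be discontinued from the study at the discretion of the Investigator for lack of adherence to study treatment or visit schedules". Section 7.1.1 adds that an outcome visit is booked only after the subject's OBVAT sessions are all done.

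On expected loss, section 6.4 speaks of "adjusting for an 80% retention rate and 15% data loss due to motion artifacts during fMRI experiments" and says that "approximately 200 subjects will be enrolled to produce 150 subjects who finish the protocol" with usable data.

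**The concern.** The protocol fixes both rules itself, so the conflict is not a detail left to a statistical analysis plan. Anyone writing the analysis program must break one of them.

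The exclusion also goes further than ordinary missing data. Outcome Visit 1 closes the only period in which the arms differ as OBVAT plus SCC versus SCC alone; afterwards arm 2 also receives OBVAT. A subject who attends that visit and withdraws later has a complete randomised outcome for the main question. Section 4.3.1 discards it because of something that happened after it was measured.

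At stake is the protection that randomisation gives. If the reasons for withdrawing are related to outcome and differ between arms, a comparison of non-withdrawers can show a difference where there is none, or hide a real one.

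**Working it through.** **1. The rules side by side.** Take a subject randomised to arm 2 who attends Outcome Visit 1 and withdraws during the later OBVAT phase. Section 6.3.2 includes this subject and the observed change. Section 4.3.1 excludes the change. Section 4.3.1 makes no exception for the primary analysis, and no other section reconciles the two. The abstract names a different primary endpoint (reduction in visual symptoms), but that is also a change over time, so the conflict is the same.

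**2. How many subjects.** Section 6.4 gives 80% retention, so 20% loss: 0.20 × 200 = 40 of the 200 enrolled, or 0.20 × 50 = 10 per arm at the 50 per arm of the power calculation. Going from 200 to 150 is a 25% loss (150/200 = 0.75), but it includes scans lost to motion. Not every non-retained subject will have chosen to withdraw, so one fifth is an upper figure for the sentence as worded. The 46 per arm in section 6.4 cannot be reproduced, because no mean differences are given; this point does not depend on it.

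**3. Could loss differ by arm?** Session load (section 4.2):

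| Period | Arm 1 | Arm 2 |
|---|---|---|
| Up to Outcome Visit 1 | 12 | 0 |
| Outcome Visit 1 to 2 | 4 | 16 |

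The load falls on arm 1 first and on arm 2 later. Illustration, assuming a constant weekly dropout hazard over the phase lengths in section 3.3.1 (6 + 2 = 8 weeks in arm 1, 6 + 8 = 14 weeks in arm 2) and average retention of 80%: solving (e^(−8h) + e^(−14h))/2 = 0.80 gives h = 0.0205. Loss is then 1 − e^(−8h) = 15.1% in arm 1 and 1 − e^(−14h) = 24.9% in arm 2. Of these, 3.5% and 13.4% are lost after week 6, when an Outcome Visit 1 value could already be in hand. A different hazard, concentrated in the first six weeks of therapy, would put the larger loss in arm 1.

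**4. What that could do to the test.** Assumptions: no true effect, 50 randomised per arm, outcome SD of 1, and correlation c between the outcome and the tendency to stay. With a share d lost, the mean of those retained shifts by c·φ(z_d)/(1 − d); for d = 0.20 this is c × 0.280/0.80 = 0.350c. The bias b is the difference between the arms' shifts, SE = √(1/n₁ + 1/n₂) on retained subjects, and type I error = 1 − Φ(1.96 − b/SE) + Φ(−1.96 − b/SE).

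| Loss, arm 1 / arm 2 | Retained | SE | Size of b | Type I error at c = 0.25, 0.5, 1 |
|---|---|---|---|---|
| 20% / 20%, same selection | 40 / 40 | 0.224 | 0 | 5.0%, 5.0%, 5.0% |
| 15% / 25%, or the reverse | 42.5 / 37.5 | 0.224 | (0.424 − 0.274)c = 0.15c | 5.3%, 6.3%, 10.2% |
| 20% / 0% | 40 / 50 | 0.212 | 0.350c | 7.0%, 13.1%, 37.8% |
| 20% / 20%, opposite selection | 40 / 40 | 0.224 | 0.700c | 12%, 35%, 88% |

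In the second row the sign of the bias follows the arm with the larger loss. The third row averages only 10% loss, which is not the protocol's 80% retention, and c = 1 means that dropout is fully determined by outcome. None of the rows is a forecast or a bound.

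**The case against.** A reader might infer that the rule biases the trial in favour of OBVAT, because only arm 1 has therapy to tire of in the first six weeks. The documents do not support that. The exclusion applies to withdrawal at any time, arm 2 carries 16 sessions against 4 after Outcome Visit 1, and the constant-hazard illustration puts the larger loss in arm 2. No dropout rates by arm are given.

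A reader might also infer that every withdrawal triggers the exclusion. The sentence names only subjects who choose to withdraw. Discontinuation by the investigator and withdrawal for scan safety are separate routes, and the protocol does not say whether their data are kept. Nor are data destroyed: they are left out of the final analysis, and baseline values serve the comparison with TYP-CI and controls.

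The fMRI withdrawal rule can fairly be read as applying to NJIT subjects only, since scanning is done only there. It is unclear in its reach, but it is not part of the contradiction.

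The choice of repeated-measures model may be left to a statistical analysis plan. That does not rescue the protocol, because the conflict is over which data may be used at all. The exclusion might be meant to honour requests that data not be used, but the sentence does not limit itself to such requests.

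**Conclusion.** The contradiction is certain: sections 4.3.1 and 6.3.2 cannot both be followed for a subject who chooses to withdraw, and the primary endpoint is exactly the kind of data that section 4.3.1 removes. It is also certain that the rule discards Outcome Visit 1 values already observed. Up to about one fifth of subjects could be affected, on the protocol's own retention figure.

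The consequence for the result is open. Depending on assumed dropout and selection, the type I error ranges from an undisturbed 5.0%, through about 5% to 10% for a 15% versus 25% split in either direction, to 38% if a fifth of arm 1 only is lost and loss is fully determined by outcome. Equal loss with opposite selection could be worse still. These figures rest on assumptions that the protocol neither states nor excludes. The point must be fixed because it decides who is in the primary analysis, not because a particular bias has been shown.

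**What to change.** 1. Replace the exclusion sentence in section 4.3.1 with: *All data collected up to withdrawal are kept and analysed in the randomised arm.* State that this covers withdrawal by the subject and by the investigator.
2. In section 6.3.2, say that all randomised subjects are analysed with a repeated-measures method that uses incomplete records, and that an analysis of completers is reported only as a sensitivity analysis. Classical repeated measures ANOVA, which that section now names, needs complete records.
3. Reconcile section 7.1.1 with the intention-to-treat rule, so that the Outcome Visit 1 clinical measures are sought from every subject still in the study, whether or not therapy was completed. Without this, the first change cannot work for arm 1, the only arm with sessions to finish before that visit.
4. Clarify in section 4.3.1 whether the scan-safety withdrawal ends scanning only or all follow-up, given that fMRI is done only at NJIT and is not part of the section 6.1 endpoint.

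The cost is protocol wording and a few clinic assessments that are already in the schedule. No change in sample size follows from this point.

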## **5 STUDY EVALUATIONS AND MEASUREMENTS**

### **5.1 Screening and Monitoring Evaluations and Measurements**

#### **5.1.1 Medical Record Review (case subjects)**

- Medical record number
  - Name
  - Email address
  - Phone number
  - Date of birth
  - Age
  - Sex
  - Zip code
  - Race
  - Ethnicity
  - Insurance
  - Provider
  - Vitals (height, weight, BP and HR if obtained clinically)
  - Date of visits
  - Concussion history
  - Medical history
  - Family medical history (family members not directly identified)
  - Medications
  - Symptoms (pre-injury, initial, and current)
  - Injury details
  - Activity history
  - Clinical examination
-

- Other concussion assessments administered clinically
- Clinical notes (i.e. return to school/exercise/sports, compliance with therapies, treatment plan)
- Physical therapy notes (if attending therapy at one of the sites or notes scanned into the medical record)

### **5.1.2 Imaging (NJIT clinical Site Only)**

Subjects will undergo fMRI imaging exams at the Rutgers University Brain Imaging Center. As previously noted, brain imaging data will be obtained from the participants in arm 1 twice and those in arm 2 three times. All subjects will be screened for contraindications for MRI prior to entering the magnet each time.

#### **5.1.2.1 Functional Magnetic Resonance Imaging Protocol**

Magnetic resonance imaging will be performed using an MRI at the Rutgers University Brain Imaging Center (RUBIC). All MRI systems to be used are FDA-approved systems and are capable of clinical use. All MR pulse sequences are FDA-approved. MRI safe vision correction lenses (Psychology Software Tools, Sharpsburg, PA) will be provided to subjects who need refraction to see the fMRI tasks. The corrective lenses and frame are made completely of plastic. All brain MR images will be read by board certified pediatric neuroradiologists, and all clinically significant incidental findings will be communicated to the participants by the study investigator.

The imaging experiment will have a magnetization-prepared rapid acquisition gradient-echo (MPRAGE), approximately 21 minutes of eye movement experiments, approximately 7 minutes of resting state data collected, and an approximately 7 minute arterial spin labeling (ASL) sequence. Participants will be given breaks between scans and eye movement experiments. Participants will have their eye movements recorded using an MR compatible EyeLink eye tracker because it is permanently installed in the scanning room.

Eye movement imaging experiments include sustained fixation, vergence steps and saccadic eye movements.

#### **5.1.2.2 Pregnancy Testing**

A urine pregnancy test will be performed for female subjects who are physically capable of becoming pregnant.

### **5.1.3 Other Evaluations, Measures**

- **Clinical Examination:** A standard optometric clinical exam that includes near point of convergence, positive fusional vergence, dissociated phoria, corrected visual acuity, unilateral cover test, stereopsis, monocular amplitude of accommodation, accommodative facility, vergence facility at near and far, negative fusion vergence, and eye movement and vestibular evaluation will be performed by a practicing, licensed optometrist.
  - **Patient-Reported Outcome Surveys:**
-

- CISS-Con
  - Vision Quality of Life with Time Survey (VisQual-T)
  - **VET:** An ISCAN eye tracker integrated into an Oculus head mounted display DK2 will track and record subjects' eye movement. The VET is about a 20 minute protocol comparing vergence steps at the beginning and end of a test while performing vergence steps and ramps, and saccades.
  - **VRS3:** An ISCAN eye tracker integrated into an Oculus head mounted display DK2 will track and record subjects' eye movement. The VRS3 is about a 15 minute protocol of vergence ramps, vergence steps, and saccades objective eye movements.
  - **Intervention:** This study involves a therapeutic intervention testing the effect of OBVAT in adolescent and young adults with PPCS-CI. Subjects will be randomly assigned to either an SCC+OBVAT or SCC only group using a pre-determined block randomization procedure.
    - **SCC+OBVAT:** subjects assigned to the SCC+OBVAT arm will attend bi-weekly OBVAT sessions with a trained and certified vision therapist. OBVAT has four phases. The first phase will be designed to manage some of the visual/vestibular issues common in PPCS-CI using eye movements associated with head and body movement. In phase 2, techniques will be used to stimulate gross convergence, positive fusional vergence and monocular accommodative therapy using Brock string, Vectograms, Computer Orthoptics and Lens Accommodative Rock, respectively. Once the subject can perform these tasks with ease, s/he will graduate to the third phase which is ramp fusional vergence and monocular accommodative therapy with Vectograms, Aperture Rule, Lifesaver Cards and Lens Accommodative Rock. The final stage will consist of jump fusional vergence and binocular accommodative facility. The initial phase is used to remediate vestibular issues if present but if there are no vestibular issues, then this phase will be omitted.
    - **SCC only:** subjects assigned to the SCC only arm will be instructed to follow care instructions of their treating physician. SCC typically consists of physical and cognitive rest immediately following the injury for a brief period of time to allow symptoms to abate, followed by a gradual re-introduction of academic and physical activities, restricting activities at high risk for repeat brain injury (such as contact or collision sports) until a graded return to play protocol has been completed without provoking symptoms. For those patients who still have vestibular signs and symptoms persisting beyond 1-month post injury, initiation of vestibular and balance rehabilitation physical therapy (VBT) may occur, as determined by the physician with the goal of improving motion tolerance and balance through exercises that include adaption by retraining the vestibular ocular reflex. While some physical therapists incorporate pencil pushups or Brock string (common
-

treatments for CI) into their VBT protocols, they will be instructed specifically not to include any convergence exercises targeting CI.

- ***Home reinforcement:*** Subjects will be instructed on in-home reinforcement while they are completing their OBVAT intervention. The home reinforcement will utilize the HTS software. Subjects will be provided the HTS software in the form of a USB drive or a CD. HTS stimulates disparity convergence and sequences the therapy from ramp to step vergence demands, always providing immediate and accurate feedback to the patient, which has been shown to improve vision function. The HTS software also allows the investigator to monitor compliance and performance with the prescribed treatment by logging the number and time of sessions.

## **5.2 Efficacy Evaluations**

### **5.2.1 Diagnostic Tests, Scales, Measures, etc.**

Subjects will complete an optometric examination, vision assessments, fMRI (NJIT clinical site only) and symptom report at all assessment visits (except arm 1 will not perform an fMRI at the second outcome). Data obtained from these assessments will be tracked and compared between the start and end of the treatment phase for all case subjects enrolled in the study, regardless of treatment arm.

## **5.3 Safety Evaluation**

This is a minimal risk study. The Principal Investigator will be responsible for monitoring the safety of study subjects and complying with all reporting requirements. The PI and study investigators will monitor data accuracy and identify ways to resolve any problem areas. A trained and certified vision therapist will monitor all subjects during OBVAT.

The effects of an MRI on pregnancy or a fetus are known to be potentially harmful from laboratory animal and from human studies. For this reason, subjects undergoing an MRI procedure should not be pregnant at the time of the study. Therefore, subjects who are menstruating will follow CHOP or Rutgers Radiology policies regarding pregnancy testing for the MRI based on where their MRI is performed.

---

## **6 STATISTICAL CONSIDERATIONS**

### **6.1 Primary Endpoint**

The primary endpoint will be the change in composite clinical parameters of near point of convergence and positive fusional vergence between the initial assessment and the outcome visits.

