### Objectives:

The primary objective of this study is to compare the effectiveness of SCC plus OBVAT compared to SCC only. The secondary objectives are to determine the underlying neural mechanism of OBVAT administered to patients with PPCS-CI as well as to compare the neural mechanistic differences between TYP-CI and PPCS-CI.

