### Study Interventions and Measures:

This study will compare the outcomes of adolescents and young adults with persistent post-concussive symptoms with convergence insufficiency who are randomized to standard-community concussion care (SCC) plus office-based vergence/accommodative therapy (OBVAT) versus those randomized to SCC alone to evaluate the effect of OBVAT in adolescents and young adults with PPCS-CI.

The primary endpoint of this study is the reduction in visual symptoms. This study will also assess the change in vision function measures and fMRI results of those that perform OBVAT compared to those who complete SCC. Additionally, this study will also assess the dose response of 12 OBVAT sessions as compared to 16 sessions.

---

---

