| Study Objective(s)                                                     | 
Primary
 
 
To compare the effectiveness of SCC plus OBVAT compared to SCC only.
 
 
Secondary
 
 
To determine the neural mechanism of OBVAT for PPCS-CI compared to SCC
 
To determine the effectiveness of 12 one-hour sessions compared to 16 one-hour sessions of OBVAT.
 
To compare the differences between PPCS-CI and TYP-CI.
 
                                                                                                                                                                                                                                                   |
| Test Article(s)
(If Applicable)                              | Office-based vergence/accommodative therapy plus standard-community concussion care vs. standard-community concussion care alone.                                                                                                                                                                                                                                                                                                                                                                                                                                                                                                                                                                                          |
| Study Design                                                           | Randomized controlled trial. Phase I                                                                                                                                                                                                                                                                                                                                                                                                                                                                                                                                                                                                                                                                                       |

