### **2.1 Primary Objective (or Aim)**

The primary objective of this study is to determine the neural mechanistic differences between PPCS-CI and TYP-CI.

---

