## **2.2 Secondary Objectives (or Aim)**

The secondary objectives are to:

- Determine the underlying neural mechanism of OBVAT administered to PPCS-CI patients.
- Compare the effectiveness of standard-community concussion care (SCC) plus 12 vs.16 one-hour OBVAT sessions compared to SCC alone.

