### **6.2 Secondary Endpoints**

Secondary endpoints will include the rate of symptom remediation in OBVAT+SCC group compared to SCC alone, change in vision function, and fMRI measures over the duration of the intervention.

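### The protocol contradicts itself on its primary objective and its primary endpoint, and nothing in it says which version prevails

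*Protocol*

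**What the plan says.** **Objective.** The abstract (Objectives) says: "The primary objective of this study is to compare the effectiveness of SCC plus OBVAT compared to SCC only". It puts the neural comparison among the secondary aims: "as well as to compare the neural mechanistic differences between TYP-CI and PPCS-CI". The synopsis agrees and lists under Primary: "To compare the effectiveness of SCC plus OBVAT compared to SCC only". Section 2.1 says something else: "The primary objective of this study is to determine the neural mechanistic differences between PPCS-CI and TYP-CI". Section 2.2 then places effectiveness among the secondary objectives: "Compare the effectiveness of standard-community concussion care (SCC) plus 12 vs.16 one-hour OBVAT sessions compared to SCC alone".

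**Endpoint.** The abstract (Study Interventions and Measures) says: "The primary endpoint of this study is the reduction in visual symptoms". Section 6.1 says: "The primary endpoint will be the change in composite clinical parameters of near point of convergence and positive fusional vergence between the initial assessment". Its sentence goes on to refer to the outcome visits in the plural. Section 6.3.2 repeats that endpoint. Section 6.2 ranks symptoms lower: "Secondary endpoints will include the rate of symptom remediation in OBVAT+SCC group compared to SCC alone". The synopsis row on efficacy evaluations lists symptoms first but does not rank its entries.

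**Tests and multiplicity.** The synopsis row on the statistical plan names a Wilcoxon signed test and a paired *t*-test. It also promises an adjustment for multiple comparisons at a 0.05 level, without a procedure. Section 6.3.2 names a repeated measures ANOVA and a chi-squared test for the primary endpoint.

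**The concern.** What is primary in one part of the protocol is secondary in another, for the objective and the endpoint alike. All of it is current text. A reader who follows the abstract and one who follows sections 2 and 6 would judge the same results by different criteria. A favourable symptom result with no difference in near point of convergence (NPC) and positive fusional vergence (PFV), or the reverse, would count as success under one part and failure under the other.

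The two objectives also describe different studies. Effectiveness is a comparison of the randomised arms. The section 2.1 objective compares enrolled patients with TYP-CI data already collected (section 4.3.1). It makes no use of the randomisation, and it depends on fMRI done at one clinical site only.

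**Working it through.** **1. The rankings side by side**

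| Item | Abstract and synopsis | Sections 2 and 6 |
|---|---|---|
| SCC+OBVAT versus SCC | Primary | Secondary (2.2) |
| PPCS-CI versus TYP-CI | Secondary | Primary (2.1) |
| Visual symptoms | Primary endpoint (abstract) | Secondary (6.2, 6.3.2) |
| NPC/PFV composite | Not named as an endpoint | Primary endpoint (6.1, 6.3.2) |
| Tests | Wilcoxon signed, paired *t* (synopsis) | Repeated measures ANOVA, chi-squared (6.3.2) |

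The neural objective of section 2.1 is matched by neither named primary endpoint; fMRI measures are secondary in section 6.2.

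**2. Does the time point settle it?** No. Section 6.1 leaves more than one outcome visit open. Under section 4.2, at outcome visit 1 arm 1 has had 12 OBVAT sessions and arm 2 has had SCC alone. By outcome visit 2 arm 1 has had 12 + 4 = 16 sessions and arm 2 has also had 16. Only outcome visit 1 gives a randomised contrast of OBVAT with SCC alone.

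**3. Does the sample size settle it?** Section 6.4 gives standard deviations of the difference of 19 (CISS), 2 (NPC), 19 (PFV) and 27 (fMRI beta weight), with 37, 6, 37 and 46 subjects needed. It uses 80% power, alpha 0.05, 80% retention and 15% motion loss. It states no difference to detect, so these figures can be neither confirmed nor refuted. One can only solve for the implied difference, assuming a two-sided test and the normal approximation:

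δ = SD × (1.960 + 0.842) / √(n × 0.80 × 0.85)

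- CISS and PFV: 19 × 2.802 / √25.16 = 10.6
- NPC: 2 × 2.802 / √4.08 = 2.8
- Beta weight: 27 × 2.802 / √31.28 = 13.5

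Without the loss adjustment the values are about 8.8, 2.3 and 11.2. The four measures are sized separately and nothing is given for an NPC/PFV composite. The governing 46 per arm (rounded to 50) comes from the beta weight, a secondary measure in section 6.2. The calculation therefore points to neither named primary endpoint.

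**4. What the ambiguity is worth.** Suppose either named primary endpoint (symptoms, or NPC/PFV) could be taken as decisive, each tested at two-sided 0.05. The document does not state sidedness.

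- Independent endpoints: 1 − (1 − 0.05)² = 1 − 0.9025 = 0.0975.
- Correlated endpoints, by simulation of two standard normal statistics (one million draws, counting either |Z| > 1.96): 0.095 at correlation 0.3, 0.091 at 0.5 and 0.078 at 0.8.
- One endpoint fixed in advance: 0.05.

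The correlations are assumptions. Section 6.4 does give correlations from pilot data, but it reports them one per measure and they are not correlations between symptoms and NPC/PFV.

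**The case against.** The strongest reply is that a statistical analysis plan, not shown here, may fix one endpoint, one test and one visit before analysis. That is fair as far as it goes. A reader might infer that the sponsor can, or will, pick the primary endpoint once the results are known. The documents do not support that, because it depends on a plan nobody here has seen. What stands is narrower: the protocol itself makes two incompatible primary declarations, and whichever one an analysis plan adopted would contradict part of the protocol.

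Three further points have weight.

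- The synopsis does promise a multiplicity adjustment, so it would be wrong to say the error rate is ignored. But the promise follows a sentence on post-hoc tests, names no method and does not rank the endpoints.
- The two tests in section 6.3.2 can be read as one continuous analysis plus a responder analysis against published benchmarks, and choosing between them is often left to an analysis plan. On its own this is minor. The conflict with the synopsis tests is not explained that way.
- It is tempting to treat NPC and PFV as safe from bias and symptoms as not. Optometrists are described as blinded (sections 3.2 and 9.1.2), while symptoms are self-reported with no sham in the comparator arm. But patients know their arm for both kinds of measure, and section 1.3 itself describes conventional clinical measurements as often subjective. The blinding favours NPC/PFV without making it immune.

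**Conclusion.** The contradiction holds for both objective and endpoint, and it must be fixed because it concerns which result decides the trial. If either named endpoint could count, the false-positive chance is 9.75% under independence and about 7.8% to 9.5% at assumed correlations of 0.8 to 0.3, against a nominal 5%. These figures assume two-sided 0.05 for each endpoint and no effective adjustment. They describe what the protocol leaves open; they are not evidence that anyone has used it.

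A reader might count the neural measure as a third candidate and arrive at 1 − 0.95³ = 14.3%. The documents do not support that. The neural comparison is a stated primary objective but nowhere a named primary endpoint, and it tests a different null hypothesis, so a false positive there would not be a false claim that OBVAT works. Nor is there a basis for adding a further amount for the two tests in section 6.3.2, which use the same measures and would be closely related.

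**What to change.** 1. Amend sections 2.1 and 2.2 so that the randomised comparison of SCC+OBVAT with SCC is the one primary objective, as in the abstract and synopsis. Make PPCS-CI versus TYP-CI a secondary, observational aim.
2. In section 6.1 name one primary endpoint at outcome visit 1, with one deciding between-arm test. The NPC/PFV endpoint is the natural choice because the statistical section already names it and blinded optometrists measure it. The sponsor must confirm that choice and define how NPC and PFV are combined.
3. Make symptoms the first key secondary endpoint and name the instrument: eligibility and section 6.4 use the CISS, whereas the visit schedule uses the CISS-Con. Keep the chi-squared responder analysis as supportive.
4. Align the abstract's endpoint sentence and the synopsis's statistical row with sections 6.1 to 6.3.2.
5. Restate the section 6.4 sample-size basis for the chosen endpoint, including the difference to be detected. It now gives no figure for the composite and takes its governing number from a secondary fMRI measure.

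The cost is amendment wording and a restated power statement. No extra data are needed.
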